### Criteria for discontinuing or modifying allocated interventions {11b}

Both alignment techniques and the robotic arm-assisted system are already used for TKA at the site and the investigating surgeons will have overarching responsibility on the allocation of treatment for each participant. If a knee joint is unable to be satisfactorily balanced following the randomised intervention, then the surgeon may choose to proceed outside this protocol. The participant will then be excluded from the analysis and will follow the standardised care pathway. These patients will be identified as *intention to treat* in the final analysis.

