### Strategies to improve adherence to interventions {11c}

As the intervention relates to surgical technique, all strategies are focused on patient management intra-operatively. Investigating surgeons will be informed of the randomised intervention 1 day prior to surgery and pre-operative planning will be conducted an hour before analgesia. In the FA group, the final implant positions will be based off soft tissue assessment during the procedure and verified post-operatively using data from the robotic arm-assisted system. In both groups final limb alignments will also be verified using post-operative long leg weight bearing x-rays.

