### Assignment of interventions: allocation

#### Sequence generation {16a}

Participants will be recruited in a block size of 4:1, which aims to maintain balanced treatment arms over time. A master randomisation sequence will be generated prior to the start of the trial using an online random number generator (www.sealedenvelope.com). The master sequence will be maintained by the sponsor and patients will be allocated a treatment in sequential order following consent. The study team and surgeon will be notified of allocation prior to surgery.

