#### Concealment mechanism {16b}

The sponsor will maintain the master randomisation sequence and will email the allocation treatment to the research team as each patient provides consent to participate in the trial.

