#### Implementation {16c}

The research team will email the sponsor with the unique de-identified patient study number once a patient has been enrolled. The research team will inform the Investigating surgeons of the randomised intervention one day prior to surgery.

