### Assignment of interventions: blinding

#### Who will be blinded {17a}

The participants and physiotherapists will be blinded to the treatment allocation. All participants will be assigned a unique study number following a consecutive order of consent. The participant identification list will be archived at the site on a secure network in a password-protected file. The investigators and research team are unable to be blinded to the allocation due to their role in the allocation of treatment and execution of surgery.

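### Section {11b} gives unblinded surgeons overarching responsibility for allocation, which conflicts with the sponsor-held sequence in {16a} to {16c} and does not rule out an override of the assigned arm

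*Protocol article*

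**What the plan says.** Section {11b}, on discontinuing or modifying allocated interventions, notes that both techniques are already in use at the site and continues: "the investigating surgeons will have overarching responsibility on the allocation of treatment for each participant". It then gives one route out of the allocated technique: "If a knee joint is unable to be satisfactorily balanced following the randomised intervention, then the surgeon may choose to proceed outside this protocol". On what follows it says: "The participant will then be excluded from the analysis and will follow the standardised care pathway". Its last sentence nevertheless identifies these patients as intention to treat in the final analysis.

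The allocation sections describe a different chain of control:

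- {16a}: "The master sequence will be maintained by the sponsor and patients will be allocated a treatment in sequential order following consent".
- {16b}: the sponsor "will email the allocation treatment to the research team as each patient provides consent to participate in the trial".
- {16c}: "The research team will inform the Investigating surgeons of the randomised intervention one day prior to surgery". Section {11c} gives the same timing.

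Section {17a} describes the research team and the investigators as "unable to be blinded to the allocation due to their role in the allocation of treatment and execution of surgery".

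Section {20c} plans both per-protocol and intention-to-treat analyses. It also moves patients affected by randomisation errors to the arm of the treatment they received.

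**The concern.** In a randomised trial, one process must fix the arm. Sections {16a} to {16c} assign that to the sponsor's sequence, and {11b} assigns overarching responsibility for it to the surgeon. The {11b} sentence stands in the section that governs changes to the allocated intervention, so a reader will look there to learn who may change the arm.

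The surgeons are unblinded, know the arm a day ahead and have the patient's CT scan available. If one of them took the sentence at its word, the patients moved would not be a random subset. They would be knees whose anatomy the surgeon thought better suited to the other technique. The article itself treats anatomy as relevant to outcome: the background suggests that the ideal technique may differ between phenotypes, and {20b} considers phenotype subgroups.

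Two things are at stake. Patients kept as randomised after a switch dilute the contrast between functional alignment (FA) and mechanical alignment (MA). Patients excluded, or moved to the arm received, leave groups that differ by selection.

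**Working it through.** **Step 1. The sections side by side.**

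- *Who fixes the arm?* {16a} and {16b}: the sponsor, from a sequence generated before the trial starts. {11b}: the surgeons have overarching responsibility. Both cannot govern.
- *What is the surgeon's part?* {11c} and {16c}: to be informed one day before surgery. {17a}: investigators and research team jointly have a role in allocation. For the research team this fits relaying the sponsor's emails. The wording is loose for surgeons, but it gives nobody discretion over the arm.
- *When may the technique be departed from?* {11b} states one condition, failure to balance the knee following the randomised intervention. Under {11a}, balance is assessed during the operation. No section describes a change before surgery, and none excludes one.
- *How is a departure analysed?* {11b} says excluded, then labels the patient intention to treat. {20c} moves randomisation errors to the arm received. An override made before surgery is assigned to neither rule, so its handling is open.

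**Step 2. Inputs for an illustration.** From {14}: difference 14 points, SD 26, 80% power, 5% significance (two-sided assumed), 10% loss, 120 per arm. Equal arms are taken from that figure. The switching rates are assumptions.

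**Step 3. The plan's own figure.** n per arm = 2 × 26² × (1.960 + 0.842)² / 14² = 54.1, so 55 evaluable. With 10% loss, 55 / 0.9 = 61.1, so 62. The stated 120 per arm is not reproduced. That is a separate matter and does not bear on the contradiction, but it explains the spare power below.

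**Step 4. Dilution when analysed as randomised.** If shares p(FA) and p(MA) receive the other technique and take on its mean outcome, the contrast is 14 × (1 − p(FA) − p(MA)).

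- 10% in one arm only: 14 × 0.90 = 12.6
- 5% in each arm: 14 × 0.90 = 12.6
- 10% in each arm: 14 × 0.80 = 11.2
- 20% in each arm: 14 × 0.60 = 8.4

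**Step 5. Power.** Evaluable per arm = 120 × 0.9 = 108. Standard error = 26 × √(2/108) = 3.538. Power = Φ(contrast / 3.538 − 1.960).

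- No switching: Φ(3.957 − 1.960) = 97.7%
- 12.6 points: Φ(3.561 − 1.960) = 94.5%
- 11.2 points: Φ(3.166 − 1.960) = 88.6%
- 8.4 points: Φ(2.374 − 1.960) = 66.1%

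**Step 6. Per-protocol or as-received comparisons.** The bias depends on how many patients switch and how their expected scores differ from the rest. The documents give neither, so no bound can be computed.

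**The case against.** A reader might infer that {11b} permits a surgeon to switch technique before surgery with no trigger and still follow the protocol. The documents do not support that. The only departure described has a condition, and even then the surgeon is said to be acting outside the protocol. It would be odd if an unconditional switch were inside it. Section {11a} also fixes the technique for patients randomised to each arm. The disputed sentence can be read as clinical responsibility for delivering treatment, loosely worded.

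Nor do the documents show a surgeon holding the arm-specific plan the day before. Under {11c} planning takes place an hour before analgesia, although the CT scan exists earlier and planning still precedes incision. The {17a} wording fits the relay role that {12}, {16b} and {16c} give the research team, so it is weak corroboration.

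Safeguards exist. Section {18b} keeps following patients who do not meet the surgical criteria. Sections {19} and {5d} provide for review of protocol deviations. Section {11c} verifies FA implant positions from the robotic data and limb alignment in both groups by x-ray, so an actual switch could well be detected. The exclusion in {11b} may also be meant only for the per-protocol set, with the patient retained under intention to treat.

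All of this stands as a limit on the point. It does not remove the conflict over who controls allocation. The benign readings have to be supplied by the reader, and follow-up and deviation review do not settle which arm a departing patient is analysed in.

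**Conclusion.** The conflict between {11b} and {16a} to {16c} is real and should be corrected. The supportable conclusion is that the wording does not rule out an override by an unblinded surgeon. It does not show that an override is authorised or expected.

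On assumed switching of 5% to 10% in each arm, the as-randomised contrast falls from 14 to 12.6 or 11.2 points and power remains about 94.5% or 88.6%, above the planned 80%. Power drops below 80% only in the 20% illustration (66.1%). These figures assume SD 26, 108 evaluable per arm, a two-sided 5% test and a full change of mean outcome on switching. It would therefore be wrong to infer that modest switching defeats the randomised comparison, provided patients are kept as randomised. The larger risk is selection bias if departing patients are excluded or analysed as received. Its size cannot be bounded from the documents.

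**What to change.** Reconcile {11b} with {16a} to {16c}:

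1. Replace the statement on surgeons' responsibility for allocation with one saying that the sponsor-held sequence fixes the arm and the surgeons deliver it. State the surgeon's responsibility for each patient's care separately.
2. State that any departure from the allocated technique, before or during surgery, is recorded as a protocol deviation with the reason and the technique performed.
3. State that such a patient is analysed in the allocated arm in the intention-to-treat analysis, with the follow-up that {18b} already provides. Limit the exclusion in {11b} to the per-protocol analysis.
4. Optionally, reword {17a} so that it refers to relaying the allocation and performing the surgery.

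The cost is a wording amendment and one field on the surgical form. No patients or visits are added, and clinical responsibility is unchanged.

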## Introduction

### Background and rationale {6a}

Total knee arthroplasty (TKA) is an established treatment for patients with symptomatic end-stage osteoarthritis. The aim of TKA is to provide pain relief and restore function; however, published literature identifies a consistent subset of patients who are not satisfied post-operatively [1–3]. Accuracy of limb alignment, implant position and soft tissue balance are important factors that influence the outcome of TKA [4–7]. It is theorised that modern prosthesis and surgical systems with high precision could assist the surgeon in optimising these factors to an individual patient’s anatomy, which may reduce the dissatisfaction rate following TKA.

Mechanical alignment (MA) has long been the gold standard in TKA and has shown excellent survivorship of 82.3% at 25 years, indicating that most knee replacements will outlast the patient’s lifetime [8]. This technique targets a neutral limb alignment through perpendicular bone resections relative to the mechanical axis of the femur and tibia [9]. It also aims for symmetrical and balanced gaps in flexion and extension, which may require surgical release of the soft tissues [6, 10, 11]. More recently, surgeons have utilised adjustments to bone cuts to achieve balance, such as minor adjustments to femoral rotation for flexion balancing, or leaving up to 3° residual varus in the tibial cut to minimise the need for soft tissue release [12]. Surgeons following these steps often refer to the technique as adjusted mechanical alignment (aMA). A recent publication by Macdessi et al. [13] showed that only 14.6% of arthritic patients have a neutral limb alignment and neutral joint line, as defined by a window of ± 3° and ± 2°, respectively. This indicates that most patients will require surgical adjustments to achieve a goal of MA or aMA, which may alter their native bony and soft tissue anatomy. Furthermore, surgical lengthening of ligaments is a challenging component of the procedure and can be highly variable [14, 15].

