#### Plans to promote participant retention and complete follow-up {18b}

Electronic data capture will provide participants with the flexibility to complete the case report forms at their own convenience. Travel compensation for non-standard of care visits such as radiology appointments will also be provided to ensure retention is maintained. Participants who are classified as *intent to treat* but do not meet the surgical criteria will continue to be followed-up for outcome and safety purposes.

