#### Methods in analysis to handle protocol non-adherence and any statistical methods to handle missing data {20c}

A *per-protocol* and *intention to treat* analysis will be performed. In the event of randomisation errors, the participant will be converted to the study arm that represents the received treatment. The statistical model will be corrected in the event of missing data and to avoid type I error when performing multiple comparisons.

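### The protocol says knees that cannot be balanced as randomised are excluded from the analysis, then labels the same patients intention to treat, without naming the set they leave

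*Protocol article*

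**What the plan says.** The protocol article deals with these patients in three places.

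- **Section {11b}** (discontinuing or modifying the intervention) sets the trigger: "If a knee joint is unable to be satisfactorily balanced following the randomised intervention, then the surgeon may choose to proceed outside this protocol". The consequence follows: "The participant will then be excluded from the analysis and will follow the standardised care pathway". The next sentence reads: "These patients will be identified as *intention to treat* in the final analysis".
- **Section {18b}** (retention) says that participants classed as intent to treat "but do not meet the surgical criteria will continue to be followed-up for outcome and safety purposes".
- **Section {20c}** (non-adherence and missing data) says: "A *per-protocol* and *intention to treat* analysis will be performed". It also moves participants affected by randomisation errors into the arm whose treatment they received.

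Two other sections bear on the point. Section {17a} (blinding) says: "The investigators and research team are unable to be blinded to the allocation due to their role in the allocation of treatment and execution of" the operation. Section {6a} (background) says: "Accuracy of limb alignment, implant position and soft tissue balance are important factors that influence the outcome of TKA".

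**The concern.** Intention to treat means that everyone randomised is analysed in the arm to which they were allocated. A patient excluded from the analysis cannot also belong to that population. Section {11b} makes both statements about the same people without saying which analysis they leave. Two analysts could follow the text and compare different populations.

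The exclusion sentence, taken as written, has three properties that matter for bias. It acts after randomisation. It depends on a choice by a surgeon who knows the arm. Its trigger, failure to balance the knee, arises under the allocated technique and concerns a factor that the protocol itself links to outcome. At stake is whether the comparison of 24-month FJS keeps the protection of randomisation.

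**Working it through.** **1. The statements side by side**

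| Section | Statement | Fits exclusion from all analyses? | Fits exclusion from per-protocol only? |
|---|---|---|---|
| {11b}, exclusion sentence | Excluded from the analysis, no set named | Yes | Only if a set name is supplied by the reader |
| {11b}, next sentence | Identified as intention to treat in the final analysis | No | Yes |
| {18b} | Outcome and safety follow-up continues | Poorly: outcome data would have little use | Yes |
| {20c} | Both analyses will be performed | No | Yes |
| {20c}, randomisation errors | Moved to the arm of the treatment received | Separate departure from intention to treat | Separate departure from intention to treat |

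The per-protocol-only reading fits best, but it has to be inferred. The article neither defines the two sets nor says which is primary.

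**2. Size of the bias if the exclusion sentence is applied literally**

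The plan gives no figure for this, so there is none to reproduce. Let p be the fraction of an arm excluded and d the number of FJS points by which the excluded patients score below those retained, whose mean is M.

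- Mean of the whole arm: (1 − p)·M + p·(M − d) = M − p·d.
- Shift from dropping them: M − (M − p·d) = p·d.
- Bias in the between-arm difference: p₁·d₁ − p₂·d₂.

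Both p and d are assumptions. With d = 20:

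- p = 5%: 0.05 × 20 = 1.0 point in that arm.
- p = 10%: 0.10 × 20 = 2.0 points in that arm.
- 10% in one arm and 5% in the other: 2.0 − 1.0 = 1.0 point net.
- Equal p and d in both arms: zero net.

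**3. Effect on the test, worst case of one arm only**

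Inputs from section {14}: SD 26, 120 per arm, 10% loss, hence 120 × 0.90 = 108 evaluable per arm; α = 0.05, taken as two-sided. The standard error is 26·√(1/108 + 1/[108(1 − p)]), and the type I error is Φ(b/SE − 1.96) + Φ(−b/SE − 1.96) with b = p·d.

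| p (one arm) | d | b | SE | Type I error |
|---|---|---|---|---|
| 5% | 14 | 0.7 | 3.58 | 0.054 |
| 5% | 20 | 1.0 | 3.58 | 0.059 |
| 10% | 14 | 1.4 | 3.64 | 0.067 |
| 10% | 20 | 2.0 | 3.64 | 0.085 |
| 10% | 26 | 2.6 | 3.64 | 0.110 |

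Power for the 14-point effect in section {14} is 0.977 with 108 per arm and 0.971 when 10% of one arm is dropped. The issue is bias, not precision.

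**The case against.** The strongest reply is that the two sentences in {11b} are adjacent and should be read together: out of per-protocol, kept in intention to treat. Sections {18b} and {20c} support this. It may well be what was meant, and it makes an error of wording more likely than an error of intent. It does not remove the defect, because the exclusion sentence is unqualified. Nor is this simply detail left to an analysis plan: the article makes a positive statement that conflicts with its own next sentence.

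Four stronger readings are tempting, and the documents do not support them.

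- **These patients will certainly be lost from every analysis.** The next sentence and the continued follow-up point the other way.
- **Exclusions will differ between arms**, because functional alignment allows wider component limits than mechanical alignment. The intervention description in {11a} gives both arms the same next step, soft tissue release, when balance is not achieved. No rate is given for either arm, so a difference is conjecture.
- **The bias could never be examined afterwards.** Section {18b} keeps these patients in outcome follow-up, so the comparison can be run with and without them.
- **The exclusions use up the 10% loss allowance and threaten power.** The inputs in {14} give 2 × 26² × (1.960 + 0.842)² / 14² ≈ 54.1, so 55 per arm, and 55/0.90 ≈ 61.1, so 62 after loss. The plan has 120 per arm. Why 120 is stated is a separate question.

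It is also fair to say that the illustrated shifts are modest beside a 14-point effect, and that similar losses in both arms would largely cancel.

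**Conclusion.** The contradiction stands as one of wording with a real consequence. Section {11b} gives an unqualified post-randomisation exclusion, decided by an unblinded surgeon, for a reason plausibly related to outcome. It then assigns the same patients to intention to treat. The probable intent is exclusion from per-protocol only, but the text does not settle it and leaves the analysed population open to choice after results are known.

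The size and direction of any bias are unknown. The shift of 1 to 2 points in one arm rests on an assumed 5% to 10% excluded and an assumed 20-point deficit; the net effect is the difference between the arms and could be near zero. The link between failure to balance and outcome is an inference, supported by the protocol's own background statement on soft tissue balance. If all randomised patients are kept in their allocated arm, bias from this source is zero.

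**What to change.** 1. In {11b}, replace the exclusion sentence and the one after it with text to this effect: such participants stay in their randomised arm in the primary all-randomised (intention-to-treat) analysis and are omitted only from the per-protocol set; their 24-month FJS is collected as for everyone else.
2. In {18b}, describe these participants as protocol deviators, so that intent to treat is not used as a label for them.
3. In {20c}, reconcile the rule that moves randomisation errors to the treatment received with the intention-to-treat analysis; analysis by treatment received can be kept as a separate, named analysis.
4. Report, by arm, how many participants were treated outside the protocol and why.

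The cost is wording and one reporting table. Section {18b} already provides for outcome follow-up, the sample size does not change, and no surgical rule is affected.

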### Strategies to improve adherence to interventions {11c}

As the intervention relates to surgical technique, all strategies are focused on patient management intra-operatively. Investigating surgeons will be informed of the randomised intervention 1 day prior to surgery and pre-operative planning will be conducted an hour before analgesia. In the FA group, the final implant positions will be based off soft tissue assessment during the procedure and verified post-operatively using data from the robotic arm-assisted system. In both groups final limb alignments will also be verified using post-operative long leg weight bearing x-rays.

### Provisions for post-trial care {30}

All participants will continue standard post-operative care with their surgeon at their conclusion of the trial. The sponsor, Stryker New Zealand Ltd, has met the Health and Disability Ethics Committee required for up-to-date insurance for injuries occurring as a result of participation in the trial. Compensation for other injuries will be covered under the New Zealand Accident Compensation Act (2001).

